### Patient population

The target population consists of medically low-risk pregnant women of different races/ethnicities. In our retrospective cohort study published in 2012, our study population in the comparison group included 45.8% non-Hispanic White, 25.5% non-Hispanic Black, 22.2% Hispanic and 6.5% “Other” race/ethnicity [21]. We expect that our current study population will be similar.

To be eligible for this study, women will 1) be between 14–45 years of age, and 2) enter prenatal care before their 20^th^ week of gestation. Study exclusion criteria include 1) medical complications of pregnancy which would preclude prenatal care provision by nurse practitioners or participation in group care (e.g. pre-gestational diabetes, severe chronic hypertension, active pulmonary tuberculosis, massive morbid obesity or severe psychiatric illness), 2) multiple gestation, 3) lethal fetal anomalies, and 4) low literacy. The exclusion criteria were set to limit the study participants as low-risk patients, which is consistent with both the GPNC model design and the scope of medical practice of nurse practitioners/nurse midwives who provide GPNC. Women who have participated in this study in a previous pregnancy will also be excluded, in order to maintain independence. Based on our preliminary data, application of these criteria will result in an estimated exclusion of 10% of women for late entry to care and 8% for pre-existing medical complications. The exclusion criteria will be applied to all women before randomization. We will track demographic characteristics and reasons for exclusion for women who are ineligible for the study as well as for those who are eligible but decline participation.

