### Randomization and masking

#### Randomization

Women who are eligible for the study will be offered participation. Women who are interested in participation will have the opportunity to ask questions, confirm interest, provide consent, undergo group assignment, as well as complete the baseline data collection (Survey 1). Women who agree to participate will be randomized 1:1 to IPNC or GPNC based on computer-generated group assignment. These assignments will be stratified by race and ethnicity (Black, White, Hispanic, Mixed, and Other).

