### Sample size

We calculated our sample size based on Aims 1 & 2 with the primary outcome of PTB. Based on the literature and our preliminary data, the rate of PTB was approximately 10-16% of women in the traditional care setting [16]. The odds ratio of comparing PTB in GPNC to IPNC was 0.67 in the Ickovics study and 0.53 in our own study [16, 17]. Our own work also suggests that the risk difference of having PTB between Black women and White women was 1.0% in the IPNC and 2.4% in the GPNC. Taken together, it is reasonable to assume that the relative risk of PTB in the IPNC group could range from 10% to 16%. For aim 1, assuming the proportion of PTB rate of 13%, our study will need *N* = 2,712 (1,356 in each group) to detect the relative risk of PTB in GPBC vs. IPNC of 0.70 with an alpha of 0.05 and a power of 90%. For aim 2, assuming the proportion of PTB rate of 0.02, our study will need *N* = 2,748 (1,374 in each group) to detect reduction in risk difference of 1.4% between Black and White women in GPNC vs. IPNC group with an alpha of 0.05 and a power of 90%. With an estimated 15% attrition rate, we will target recruiting 3,160 (*N* = 1,580 in each group) women for this study. Table 3 gives the estimated minimum number (in each group) required to achieve an alpha of 0.05 and a power of 80% or 90% to detect the risk ratio from 0.5 to 0.7 in Aim 1 and to detect the risk difference from 0.01 to 0.08, given the rate difference (P_0_) of preterm birth between Black women and White women at the IPNC group ranges from 2% to 3% in Aim 2, This sample size estimates that the proposed study will have 90% power to detect racial difference on PTB for Aim 2.

**Table 3 Tab3:** Sample size and power calculations

	Power = 80%			Power = 90%		
Aim 1	RR = 0.50	RR = 0.60	RR = 0.70	RR = 0.50	RR = 0.60	RR = 0.70
P_0_ = 0.10	435	721	1,356	582	965	1,814
P_0_ = 0.13	326	540	1,014	436	723	1,356
P_0_ = 0.16	258	427	800	345	571	1,070
Aim 2	RD = 0.01	RD = 0.014	RD = 0.018	RD = 0.01	RD = 0.014	RD = 0.018
P_0_ = 0.02	2,319	1,027	526	3,103	1,374	704
P_0_ = 0.03	3,826	1,799	995	5,121	2,048	1,332
P_0:_ the RD of PTB in IPNC group; RR: relative risk						

Abbreviation: RD = risk difference

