### Analytic plan

Primary analyses for Aims 1, 2, and 3 will be conducted using an intent-to-treat approach. Study participants will be retained in their original assignment groups after the randomization in the analysis regardless of the number of missed visits, the use of additional services (e.g., progesterone), or loss to follow-up.
*Aim 1 analysis plan*: comparison of primary and secondary outcomes for GPNC vs. IPNC. To test the hypothesis for aim 1 that women who participated in GPNC will have a lower rate of PTB and other selected birth outcomes as compared to their counterparts in IPNC, multivariate regression models (logistic regression if the outcome is a binary variable and linear regression if the outcome is a continuous variable) will be employed with the intervention assignment as the primary independent variable. We will test the null hypothesis of coefficient of main exposure variable (GPNC vs. IPNC) equals zero. Stratified analyses will be conducted (e.g. race/ethnicity, previous history of PTB) to compare the primary and other outcomes within sub-groups.
*Aim 2 analysis plan*: comparison of racial disparities of primary and secondary outcomes for GPNC vs. IPNC. To test the hypothesis for Aim 2 that the Black-White differences in PTB and other selected birth outcomes is smaller in the GPNC as compared with that in IPNC, we will apply analyses similar to Aim 1 but adding an interaction term of prenatal care (GPNC vs. IPNC) with race (White vs. Black). We will test the null hypothesis of coefficient of interaction term equals zero. For aim 2, only women identified themselves as either Black or White will be included in the primary analysis. Then, we will conduct a sensitivity analysis to see whether including women who self-identified race as “Hispanic ethnicity”, “Mixed race” and “Other race” will influence the primary analysis results. Such sensitivity analysis will be guided by the results from the sub-groups analysis in Aim 1.

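### Aim 2 is sized on all randomised women, but its primary analysis keeps only Black and White women (about 71%), so the claimed 90% power does not apply to the women analysed

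*Protocol article*

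**What the plan says.** The Sample size section sets the Aim 2 requirement with the inputs "For aim 2, assuming the proportion of PTB rate of 0.02" and an effect worded as "to detect reduction in risk difference of 1.4% between Black and White women in GPNC vs. IPNC group". With alpha 0.05 and 90% power it arrives at 2,748 women, 1,374 per group. It allows 15% for attrition, sets the recruitment target at 3,160, and concludes: "This sample size estimates that the proposed study will have 90% power to detect racial difference on PTB for Aim 2".

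The target covers women of all races. Under Patient population, the earlier cohort's comparison group was "45.8% non-Hispanic White, 25.5% non-Hispanic Black, 22.2% Hispanic and 6.5% “Other” race/ethnicity", and the protocol expects a similar mix here. Under Randomization, the strata are Black, White, Hispanic, Mixed and Other. Under Participant recruitment and screening, all eligible women at the site count towards 3,160.

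The Analytic plan restricts the Aim 2 primary analysis: "For aim 2, only women identified themselves as either Black or White will be included in the primary analysis". Women in the other categories enter a sensitivity analysis only.

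**The concern.** The number required for Aim 2 and the number analysed for Aim 2 refer to different sets of women. Hispanic, Mixed and Other women, about 29% of expected enrolment, count towards the 2,748 but contribute nothing to the primary test of the care-by-race interaction. The inflation covers attrition only, and no quota or enrichment raises the share of Black and White women.

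Racial disparity is a headline aim, and both Preliminary research and Specific aims present the trial as adequately powered for it. A null Aim 2 result, read against a stated 90% power, could be taken as evidence that group care does not change the disparity. The section on interim analyses also allows recruitment to stop once power reaches the desired level for each hypothesis, so a wrong Aim 2 denominator could mislead that decision too.

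The mismatch is independent of the variance formula. Whichever formula is used, the N entered is not the N analysed, and correcting the formula alone would leave the restated precision too favourable.

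**Working it through.** **Inputs.** From Sample size: 2.0% against 0.6% (0.020 − 0.014), alpha 0.05 taken as two-sided, 90% power, 15% attrition, 3,160 recruited. From Patient population: 45.8% White and 25.5% Black. From Randomization: 1:1 allocation.

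**Step 1: reproduce the stated figure.** The pooled two-proportion formula without continuity correction is

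n = [z₀.₉₇₅ √(2p̄(1−p̄)) + z₀.₉₀ √(p₁(1−p₁) + p₂(1−p₂))]² / (p₁−p₂)²

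With p₁ = 0.020, p₂ = 0.006 and p̄ = 0.013:

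- √(2 × 0.013 × 0.987) = 0.1602
- √(0.0196 + 0.005964) = 0.1599
- n = (1.960 × 0.1602 + 1.2816 × 0.1599)² / 0.014² = 1,374 per group, or 2,748 in total, an exact match
- 2,748 × 1.15 = 3,160, the recruitment target

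The larger of the two aims' requirements (2,748 against 2,712 for Aim 1) therefore sets enrolment, with no allowance other than attrition.

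**Step 2: the Aim 2 analysis set.**

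- Share: 0.458 + 0.255 = 0.713
- Enrolled: 3,160 × 0.713 = 2,253
- After attrition: 2,253 × 0.85 = 1,915, about 958 per arm (about 615 White and 343 Black)
- Shortfall: 1 − 1,915/2,748 = 30%

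**Step 3: power on the plan's own formula.** Power = Φ{[0.014√n − 1.960 × 0.1602] / 0.1599}.

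| Women analysed | Per arm | Power |
|---|---|---|
| 2,748 (as stated) | 1,374 | 90.0% |
| 2,686 (3,160 × 0.85, all races) | 1,343 | 89.3% |
| 2,253 (71.3%, no attrition) | 1,126 | 83.5% |
| 1,959 (71.3% of 2,748) | 980 | 78.1% |
| 1,915 (71.3% of 2,686) | 958 | 77.2% |

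The restriction alone takes 90.0% to 78.1%. The remaining point arises because multiplying by 1.15 does not fully offset 15% attrition.

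**Step 4: sensitivity to the race share.** After attrition, power on the same formula is 70% at a Black and White share of 60%, 82% at 80% and 86% at 90%. Even at 100% it is 89%.

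**Step 5: the contrast actually tested.** Aim 2 compares two Black-White risk differences, so its variance comes from four preterm birth rates. The protocol does not give these rates by race and arm. Assume White/Black rates of 12%/14% in individual care and 8.5%/9.1% in group care, which give risk differences of 2.0 and 0.6 points. Then

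SE = √(0.12×0.88/615 + 0.14×0.86/343 + 0.085×0.915/615 + 0.091×0.909/343) = 0.0298

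- 95% CI half-width: 1.96 × 0.0298 = 5.8 points
- Power for 1.4 points: 0.014/0.0298 = 0.47 standard errors, about 8%
- If all 2,686 retained women were Black or White in the same ratio: SE = 0.0298 × √0.713 = 0.0252, half-width 4.9 points, power about 9%

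With the overall individual-care rate varied over the protocol's 10–16% and a group-care rate 0.70 times that, power for 1.4 points at 2,686 completers, of whom 71.3% are analysed, stays at about 7–8%.

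**The case against.** The strongest objection is that the 77% has no real meaning. It comes from a formula that treats risk differences of 2.0% and 0.6% as if they were event rates. On the contrast actually tested, the restriction moves power only from about 9% to about 8%, and half-widths of 4.9 and 5.8 points are both several times the 1.4-point target. On this view the formula is the larger fault and the analysis set a detail within it.

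The formula fault is indeed larger, and 77% must not be quoted as corrected power. It does not remove this point: replacing the formula while again entering about 2,700 women would still give an interval about 0.9 points too narrow in half-width.

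Two smaller objections stand in part. The 71.3% comes from an earlier cohort's comparison group, and the handling of women who report both a race and Hispanic ethnicity is not explicit, so 1,915, 615 and 343 are approximate. The 30% shortfall also includes a small attrition component, separated in the working. Neither changes the direction, and no share from 60% to 100% restores 90%.

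The planned monitoring of power could expose the shortfall during the trial, but it does not correct the statement in the Sample size section.

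**Conclusion.** The concern holds. The Aim 2 requirement of 2,748 is met by counting women whom the Aim 2 primary analysis excludes. About 1,915 women would be analysed, 30% below the requirement, and the plan's own calculation then gives about 77% power instead of 90%. This rests on the protocol's expected race mix and 15% attrition; over shares of 60–90% the figure runs from 70% to 86%.

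For the difference of risk differences, the expected 95% CI half-width is about 5.8 points and power for a 1.4-point change is about 8%, under the assumed rates of 9–14%. The 90% claim is unsupported on either basis.

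**What to change.** In the Sample size section:

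- State Aim 2 on the set that the Analytic plan analyses: about 2,253 Black and White women enrolled and 1,915 evaluable, or about 615 White and 343 Black per arm. Give the assumed race mix and a range around it.
- Remove the sentence claiming 90% power for Aim 2. Replace it with the expected 95% CI half-width and the power for that set, both computed for the difference of Black-White risk differences with stated preterm birth rates. Do not substitute 77%, which rests on the unsuitable formula.
- State that Aim 2 will be reported as an estimate with its confidence interval, so that a null result is not read as no effect on the disparity.

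The cost is rewording and a less favourable Aim 2 statement. Enrolment stays as planned. Raising it to meet the plan's own figure would take about 2,748 / 0.713 × 1.15 = 4,432 women, or 2,748 / 0.713 / 0.85 = 4,534, and would still not give 90% power for the contrast tested.

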### Data collection

For this study, data will be collected at the following 3 time points: 1) At the time of Baseline Visit (8–23 weeks of gestational age), women will undergo group assignment and complete the baseline data collection (Survey 1); 2) After 30 weeks gestational age, research nurses will meet participants prior to or after their prenatal care appointment to administer the second survey (Survey 2); and 3) Postpartum data collection will be conducted after women attend their postpartum visit and consist of medical chart abstraction, and will not require patient contact. The study surveys will be administered electronically. Patients’ medical information will be collected from the electronic medical record (EMR). Regular data review/reports will be generated through the EMR to monitor enrollment, group balance, and the timing of the reminder calls & patient incentives. The overall timeline for study visits and data collection is summarized in Table 2.

**Table 2 Tab2:** Data collection and outcome measurement

	Gestational age <23 week (Survey 1)	Gestational age 30+ week (Survey 2)	12-week Postpartum medical chart review
Birth outcomes and pregnancy complications			
Gestational age at delivery			X
Birth weight			X
APGAR scores			X
Admission to neonatal intensive care unit (NICU)			X
Intrauterine fetal demise			X
Neonatal death			X
Pre-eclampsia			X
Gestational hypertension			X
Gestational diabetes			X
Intrauterine growth restriction			X
Macrosomia (weight >4000 g.)			X
Hospital admission during pregnancy, reason			X
Induction and reason			X
Maternal behavioral and other measures			
Maternal smoking, alcohol and marijuana use	X	X	X
Physical activity, dietary intake, and multivitamin use		X	
Maternal psychosocial measures			
Patient activation measure (PAM)	X	X	
Prenatal planning and preparation coping		X	
Prenatal anxiety, and depressive symptoms	X	X	
Shift and Persist	X		
Discrimination in prenatal care		X	
Stress management		X	
Perceived family support	X		
Support from baby’s father & relationship with baby’s father		X	
Life stressor, financial stressor and housing instability in pregnancy		X	
Perceived stress and neighborhood safety	X		
Everyday discrimination scale	X		
Role of religious on dealing with stress	X		
Adverse childhood experience	X		
Interconception care			
Attendance at postpartum visit			X
Postpartum contraception use			X
Demographics			
Race and ethnicity	X		

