*Aim 3 analysis plan*: comparison the effects of GPNC on maternal psychosocial (i.e. activation, engagement, stress) and behavioral (i.e. smoking, healthy eating, healthy practices) changes and exploring whether improving maternal psychosocial and health behavior outcomes will explain the potential benefits of the GPNC on racial disparities in birth outcomes. To address Aim 3, we will first test whether changes in maternal health behaviors or psychosocial factors differ by intervention and race. To do this, a similar analytic plan as used in Aim 1 & 2 will be applied, however, the dependent variables will be changes of health behaviors or psychosocial factors from baseline (~20 weeks) visit to late pregnancy (30–36 weeks). If we observe any significant differences in these health behaviors or psychosocial factors by intervention or race, the next step is to explore whether and to what extent the differences in the intermediate health behavior or psychosocial factors could explain the intervention effect or racial disparities of birth outcomes. To do so, the main multivariate regression models will be examined with and without adjustment for the intermediate health behavior or psychosocial variables.

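### Aim 3 takes raw change from baseline as its outcome and does not provide for the baseline value as a covariate, which costs power on the measures taken at both surveys

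*Protocol article*

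**What the plan says.** The Aim 3 analysis plan (protocol article, Analytic plan) begins: "we will first test whether changes in maternal health behaviors or psychosocial factors differ by intervention and race". For the model it says that "a similar analytic plan as used in Aim 1 & 2 will be applied", with one stated departure: "the dependent variables will be changes of health behaviors or psychosocial factors from baseline", at about 20 weeks, to late pregnancy.

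The borrowed template is in the Aim 1 and Aim 2 paragraphs of the same section. It is a multivariate regression, "logistic regression if the outcome is a binary variable and linear regression if the outcome is a continuous variable", which "will be employed with the intervention assignment as the primary independent variable". Aim 2 adds an arm-by-race interaction. No adjustment covariates are listed for any aim.

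Table 2 (Data collection) marks both Survey 1 and Survey 2 for patient activation, for "Prenatal anxiety, and depressive symptoms", and for smoking, alcohol and marijuana use. For these measures both values will be in hand.

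The mediation step is conditional on the result: "If we observe any significant differences in these health behaviors or psychosocial factors by intervention or race, the next step is to explore" whether the intermediate factors explain the birth outcomes.

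**The concern.** The template was written for preterm birth and other birth outcomes, which have no baseline value. Carried over to repeated self-report scales with only the outcome changed, it brings the baseline in by subtraction alone. That fixes the baseline coefficient at 1, whereas the regression of follow-up on baseline (equal SDs) has slope rho, the correlation between the two surveys. Whenever rho is below 1, subtraction removes too much: variance is left in the contrast, and a chance difference between arms at Survey 1 passes into the estimate with weight -(1 - rho).

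What is at stake is power. The Sample size section rests on Aims 1 and 2 with preterm birth as outcome, so nothing was planned for Aim 3. Its first-stage test is also one of the routes into the mediation analysis.

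**Working it through.** **The plan's own figure.** There is no sample size or power statement for Aim 3 to reproduce. The Aim 1 figure does reproduce: control rate 0.13, relative risk 0.70 (so 0.091), two-sided alpha 0.05, power 90%, pooled variance, no continuity correction:

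n = [1.960 × √(2 × 0.1105 × 0.8895) + 1.282 × √(0.13 × 0.87 + 0.091 × 0.909)]² / 0.039² = 1,356 per arm, as stated.

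**Inputs for Aim 3**
- Women per arm: 1,580 × (1 - 0.15) = 1,343, from the recruitment target and attrition in Sample size.
- Allocation 1:1 (Randomization and masking); two-sided alpha 0.05.
- Assumed, because the article gives neither: equal SDs at the two surveys, and rho from 0.3 to 0.8.
- Assumed effect for illustration: 0.10 SD.

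**Formulas, per woman, in SD² units**
- Raw change: V = 2(1 - rho).
- Baseline-adjusted: V = 1 - rho² = (1 - rho)(1 + rho).
- Ratio of women needed, raw change to adjusted: 2/(1 + rho).
- Standard error of the arm contrast: √(2V/1,343). Power ≈ Φ(0.10/SE - 1.96).
- Difference detectable with 90% power: (1.960 + 1.282) × SE.

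Example at rho 0.5. Raw change: V = 1.00, SE = 0.0386, 0.10/SE = 2.59, power = Φ(0.63) = 74%. Adjusted: V = 0.75, SE = 0.0334, 0.10/SE = 2.99, power = Φ(1.03) = 85%.

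| rho | V change | V adjusted | Women needed, ratio | Detectable at 90%, change vs adjusted (SD) | Power at 0.10 SD, change vs adjusted |
|---|---|---|---|---|---|
| 0.3 | 1.40 | 0.91 | 1.54 | 0.148 vs 0.119 | 59% vs 78% |
| 0.5 | 1.00 | 0.75 | 1.33 | 0.125 vs 0.108 | 74% vs 85% |
| 0.7 | 0.60 | 0.51 | 1.18 | 0.097 vs 0.089 | 92% vs 95% |
| 0.8 | 0.40 | 0.36 | 1.11 | 0.079 vs 0.075 | 98% vs 99% |

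The variance ratio is the same for the arm-by-race interaction if rho is common to the groups. At rho 0.5, an interaction that raw change detects with 80% power is detected with Φ(2.80/√0.75 - 1.96) = 90% after adjustment.

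**Is raw change biased?** Simulation at 1,343 per arm (4,000 trials per setting; rho 0.3, 0.5, 0.7) gave mean estimates for raw change of about 0 and about 0.10 when those were the true effects, and type I error of 4.8% to 5.1%. The slope of the estimate on the chance baseline difference was about -0.69, -0.52 and -0.30, close to -(1 - rho); after adjustment it was about 0. The SD of that chance difference is √(2/1,343) = 0.039, so a one-SD imbalance moves the raw-change estimate by 0.7 × 0.039 = 0.027 SD at rho 0.3 and by 0.2 × 0.039 = 0.008 SD at rho 0.8.

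These figures are for scale scores. No figure is computed for substance use, because the article does not say how it is recorded or how its change is coded.

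**The case against.** The strongest objection is that the article does not exclude baseline adjustment. It calls the models multivariate, names arm as the primary independent variable (which suggests others), and lists no covariates for any aim; such lists are often left to an analysis plan, which is not shown here. In addition, a linear model of change with baseline as covariate gives the same arm coefficient as a model of the Survey 2 value with that covariate, so the named outcome is compatible with the remedy. This stands, and a reader should not infer that the plan rejects adjustment. It does not remove the point: the outcome is fixed in the text, and what is written around it yields the less efficient test.

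Other stronger readings are tempting but unsupported:

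- **Bias or inflated type I error.** Under randomisation, raw change has neither. The imbalance effect is conditional, falls in either direction and is very small at this size.
- **A missed arm effect shuts off the mediation analysis.** The gate also opens on differences by race, and the mediation work is described as exploratory.
- **Change in substance use can only be -1, 0 or +1 and so fits neither model.** That assumes yes/no recording, which the article does not state.
- **A fixed gain in power.** It depends on rho, and at rho 0.8 it almost vanishes. The 15% attrition was set for preterm birth; no Survey 2 completion rate is given.

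**Conclusion.** The point holds as a matter of efficiency. For the Aim 3 measures taken at both surveys, the plan as written leads to an analysis that is valid on average but needs about 54% (rho 0.3) to 11% (rho 0.8) more women than a baseline-adjusted one. For an assumed 0.10 SD effect the power difference runs from about 18 points at rho 0.3 through 11 at rho 0.5 to 1 at rho 0.8. This rests on equal SDs, the assumed range of rho and 1,343 evaluable women per arm. It concerns a secondary aim and leaves the primary outcome untouched.

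Two limits apply. The Black-White comparison is not randomised; there, raw change and baseline-adjusted analyses answer different questions, so adjustment is not a plain improvement. And measures that Table 2 marks at one survey only, such as coping or perceived stress, allow neither analysis and lie outside this point.

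**What to change.** State in the Aim 3 analysis plan that, for every measure taken at both surveys, the GPNC vs IPNC comparison and the arm-by-race interaction include the Survey 1 value of the same measure as a covariate:

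- Scales: linear regression of the Survey 2 value, or equivalently of change, adjusted for the Survey 1 value.
- Substance use, where recorded as yes/no: logistic regression of Survey 2 use, adjusted for Survey 1 use.
- Raw change: kept as a descriptive summary.
- Black vs White comparison: left as it is.

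One caveat belongs with this. The Randomization and Data collection sections list group assignment before Survey 1 at the same visit, in an unblinded trial, so Survey 1 answers could be affected by knowledge of the arm. Complete Survey 1 before the assignment is disclosed, or report the order as a limitation; since recruitment had already begun, only the second is open for any women already enrolled in that order. This is no reason to prefer raw change, which would subtract the whole of such a shift, while adjustment subtracts only about rho times it.

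The cost is a sentence of text and, if adopted, a change of order at the enrolment visit. No new data, visits or participants are needed, because the Survey 1 values are already required to compute change.

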### Specific aims and hypotheses

The proposed study will employ a RCT design adequately powered to detect difference in PTB by intervention and race. The study will be conducted in a large prenatal care provider in South Carolina (SC), with historically high PTB rates of 16.4%. The proposed study builds on an established research program focused on assessing the impact of GPNC vs. IPNC on birth outcomes and will investigate the following Specific Aims:

### Specific Aim 1

To compare the rate of PTB prior to 37 weeks gestational age and other selected birth outcomes and pregnancy complications (e.g. birth weight, caesarean section rate) among women who participate in CenteringPregnancy GPNC to their counterparts in IPNC.

#### Study hypothesis 1

Women who participate in GPNC will have a lower rate of PTB and other improved birth outcomes as compared to their counterparts in IPNC.

### Specific Aim 2

To compare the risk difference of PTB and other selected birth outcomes of Black women vs. White women in GPNC to the risk differences of Black women vs. White women in IPNC.

#### Study hypothesis 2

The risk difference of PTB and other selected birth outcomes between Black and White women in the GPNC group is smaller than that in the IPNC group.

### Specific Aim 3

To compare whether women in the GPNC have improved maternal psychosocial (i.e. activation, engagement, stress) and behavioral (i.e. smoking, healthy eating, health practices) outcomes as compared to their counterparts in IPNC and to explore whether improving certain maternal psychosocial and behavioral outcomes will explain the potential benefits of GPNC on racial disparities in birth outcomes.

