#### In survey 2, all patients will complete

A subset of questions from the Pregnancy Empowerment Scale: to assess women’s engagement in their health care and in making their pregnancy healthy [61];Attendance of support people: Women will report who attended prenatal care with them in a supportive role and how often.

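### Aim 3 defines every outcome as a change from baseline, but two to four of its six named constructs are not measured at both surveys

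*Protocol article*

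**What the plan says.** Specific Aim 3 concerns "improved maternal psychosocial (i.e. activation, engagement, stress) and behavioral (i.e. smoking, healthy eating, health practices) outcomes". The Analytic plan repeats the six constructs for Aim 3, this time as "maternal psychosocial (i.e. activation, engagement, stress) and behavioral (i.e. smoking, healthy eating, healthy practices) changes", and fixes the form of the outcome: "the dependent variables will be changes of health behaviors or psychosocial factors from baseline (~20 weeks) visit to late pregnancy (30–36 weeks". If these analyses show differences by intervention or race, an exploratory step refits the main regression models with and without the intermediate variables.

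The schedule is in Table 2 under Data collection. The row "Physical activity, dietary intake, and multivitamin use" is marked for Survey 2 only, and the row "Perceived stress and neighborhood safety" for Survey 1 only. Engagement has no row in Table 2. It is assessed by "A subset of questions from the Pregnancy Empowerment Scale", listed among the items completed in Survey 2. Postpartum data come from chart abstraction without patient contact.

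On the order of events at enrolment, the Randomization section says that women "provide consent, undergo group assignment, as well as complete the baseline data collection (Survey 1"). The Study design section describes the trial as un-blinded.

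**The concern.** The outcome definition and the measurement schedule appear in the same document and do not fit together. A change from baseline can be formed only where the same instrument is given at both surveys. Where it is given once, the stated dependent variable does not exist, and no later data collection supplies the missing half. An analyst following the text would have to drop those constructs or invent another outcome after seeing the data.

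Aim 3 and the explanatory step that depends on it are at stake. The analysis plan can be reworded at any time, but a measure that was not collected cannot be recovered. Recruitment began in July 2016, so each woman who passes a survey window without the measure is lost for it.

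**Working it through.** The protocol gives no numerical figure for Aim 3 to reproduce. The check is a tally of the schedule against the outcome definition.

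**Step 1. Behavioral and psychosocial rows of Table 2 (15 rows).**

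- Both surveys (3): smoking, alcohol and marijuana; Patient Activation Measure; prenatal anxiety and depressive symptoms.
- Survey 1 only (6): Shift and Persist; family support; perceived stress and neighborhood safety; everyday discrimination; religiosity; adverse childhood experience.
- Survey 2 only (6): physical activity, diet and multivitamins; coping; discrimination in prenatal care; stress management; support from the baby's father; life, financial and housing stressors.

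3 + 6 + 6 = 15. A change can be formed for 3 rows and not for 12 (12/15 = 80%). Several Survey 1-only rows look like baseline covariates rather than outcomes. Setting all six aside leaves 15 − 6 = 9 rows with a Survey 2 value, of which 6 (6/9 = 67%) have no baseline. The table was read by program from the PDF, but its column positions are consistent from row to row.

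**Step 2. The six constructs named in Aim 3, strict reading.**

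| Construct | Survey 1 | Survey 2 | Change computable? |
|---|---|---|---|
| Activation | Patient Activation Measure | Patient Activation Measure | Yes |
| Smoking | Substance use | Substance use | Yes |
| Engagement | none | Pregnancy Empowerment Scale items | No |
| Healthy eating | none | Diet | No |
| Health practices | none | Physical activity, multivitamins | No |
| Stress | Perceived stress | Stress management; life stressors | No, different measures |

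Result: 6 − 2 = 4 of 6 not computable.

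**Step 3. Sensitivity to how constructs are mapped.**

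- The Prenatal Distress Questionnaire is listed under Study outcomes but has no row in Table 2, so its timing is unknown. If it is given at both surveys, stress is rescued: 4 − 1 = 3 of 6.
- On the most generous reading, prenatal anxiety stands in for stress, and alcohol and marijuana use count as health practices: 4 − 2 = 2 of 6. Engagement and healthy eating remain without a baseline.

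**Step 4. Order of assignment and Survey 1.** The Randomization, Data collection and Retention plan sections all mention assignment or randomization before Survey 1. None says that one must precede the other. The recruitment flow chart (Fig. 1) is not shown.

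**The case against.** The strongest reply is that little is lost. The arms are randomized, so engagement, diet and stress management can be compared at Survey 2 without any baseline. The explanatory step adjusts for intermediate variables, and nothing in its description requires them to be change scores. Aim 3 does not name the Perceived Stress Scale as its stress outcome, and Survey 1 timing suits a baseline covariate. The sample size rests on Aims 1 and 2, and the explanatory step is exploratory. All of this stands and limits the point to the stated change outcome. The contradiction remains, because the text defines all Aim 3 dependent variables as changes.

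A reader might infer three stronger things that the document does not support:

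- **That Aim 3 cannot be run for stress, engagement or healthy eating.** Only the change score fails. Late-pregnancy comparisons by arm remain available, except for the Perceived Stress Scale itself, which has no Survey 2 value.
- **That baseline answers are contaminated by knowledge of the assignment.** The text lists the events of the visit in an order but does not mandate it. This supports a request for clarification and no more.
- **That change scores waste a known amount of precision.** With equal variances, the variance of a baseline-adjusted comparison relative to a change-score comparison is (1 + r)/2, where r is the correlation between surveys. The protocol gives no r. If baseline is already a covariate in the linear model for change, the treatment estimate is identical and the loss vanishes. The covariates are not listed and may be set in an analysis plan that is not shown, so no size can be attached.

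**Conclusion.** The point holds as an internal contradiction between the Aim 3 outcome definition and the measurement schedule. The stated change is not computable for 4 of 6 named constructs on a strict reading, 3 of 6 if the Prenatal Distress Questionnaire is given at both surveys, and 2 of 6 (engagement and healthy eating) on the most generous reading. The range depends entirely on how stress and health practices are mapped to instruments, which the protocol does not spell out. Activation, substance use and anxiety or depressive symptoms can be analysed as written. The preterm birth analyses under Aims 1 and 2 are untouched. The order of assignment and Survey 1 is a secondary point about unclear wording and is not a demonstrated bias. The correction should be made, because a declared aim cannot be carried out as defined and the remedy is close to free.

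**What to change.** 1. Define each Aim 3 outcome as the Survey 2 value compared by arm, adjusted for race stratum and, where one exists, for the Survey 1 value of the same measure. Use linear regression for continuous outcomes and logistic regression for binary ones.
2. Compare measures taken only at Survey 2 directly between arms.
3. List which instrument represents each of the six constructs and which Survey 1-only items are covariates. State when the Prenatal Distress Questionnaire is given.
4. Treat perceived stress as a baseline covariate, or add the scale to Survey 2.
5. As a secondary change, state that Survey 1 is completed after consent and before the assignment is revealed.

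Items 1 to 3 cost only wording. Adding the scale costs a few minutes per participant, and women already past Survey 2 will lack it, so that outcome would be incomplete. If current practice differs from item 5, it means reordering two steps of one visit and helps only women not yet enrolled.
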